## Discussion

This study will compare the five most frequently used formulas to calculate Vc regarding their within and between-day reliability, assessed by the example of M. biceps femoris and M. rectus femoris. This study will also investigate the effect of different ISI during repeated stimulation on Vc of the same muscles.

To our knowledge, only two studies have investigated the reproducibility of Vc so far. Lohr et al. [27] investigated the within and between-day reliability of Vc_10-90%_ in the lumbar erector spinae muscle of healthy females and males. Vc_10-90%_ in this study showed an excellent relative (ICC > 0.90) and absolute (CV < 8%) reliability. De Paula Simola et a. [28] investigated the between-day reliability of Vc_10%_ and Vc_90%_ in the rectus femoris, biceps femoris, and gastrocnemius lateralis of male sports students. Vc_10%_ and Vc_90%_ both showed excellent relative reliability in all three muscles (ICC > 0.90) [28]. Absolute reliability was higher in rectus femoris and biceps femoris (CV < 10%) compared to gastrocnemius lateralis (CV = 12.3% and CV = 11.3% for V_10_ and V_90_, respectively) [28]. Our study will add to these results by contributing information on the within and between-day reliability of the five most frequently used formulas to calculate Vc. Thereby our results will allow a direct comparison between these formulas in terms of their reproducibility.

Further, information on the optimal rest interval between consecutive stimuli during progressive electrical stimulation is lacking. Again, only two studies have investigated the effect of different ISI on tensiomyographic parameters [31, 32]. One study investigated the effect of different ISI (30 s, 10 s, 5 s) on Dm and Tc of the rectus femoris muscle during ten consecutive stimuli [31]. The results showed that Tc was not significantly affected by different ISI, whereas Dm was significantly greater using an ISI of 10 s than 30 s [31]. Notably, Tc decreased significantly during ten consecutive stimuli, irrespective of the ISI, whereas Dm was not affected [31]. These findings are relevant for assessing the muscle contraction velocity using Vc. An increase in Vc can be expected, if Dm increases while Tc remains unchanged as a higher displacement amplitude is achieved within the same time. Similarly, an increase in Vc can be also expected, if Tc shortens while Dm remains unchanged, as the same displacement amplitude is achieved within a shorter time. According to Wilson et al. [31], these changes in Dm and Tc during repeated stimulation may be explained by a potentiation effect. Indeed, repeated low-frequency electrical stimulation can induce post-tetanic potentiation [56], which leads to increased peak force, decreased time to peak force and increased rate of force development during an electrically evoked twitch [57]. Thus, it is conceivable that such a potentiation effect could also lead to an increase in Vc.

In contrast, Latella et al. [32] found no significant effect of ISI (10 s, 20 s) on Dm or Tc of the biceps brachii muscle, measured across three different joint angles and two days. Consequently, they concluded that an ISI of 10 s is sufficient during five consecutive stimuli to avoid the effects of fatigue or potentiation. However, both studies did not report Vc, so the effect of ISI during repeated stimulation on Vc is still unclear. Therefore, our results will contribute relevant information on methodical considerations for the determination of Vc using TMG.

A certain limitation of our study is that we will only assess two different muscles of the lower extremities. In the future, the reproducibility of Vc and the effect of changing ISI on Vc should therefore be investigated in a broad range of muscles, including muscles of the upper extremities. Another limitation of our study is that we will include only healthy and physically active women and men between 18 and 40. The effect of different ISI on Vc might differ in older subjects or athletes due to age- and training-related shifts in the muscle fibre spectrum [11, 58, 59].

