As a result, an increasing number of studies reports the rate of displacement (Vc), i.e. the slope of the radial displacement-time curve. Several different formulas exist to calculate Vc but no consensus exists on the most suitable formula. Further, there is a lack of studies investigating the reproducibility of these formulas, as only two studies investigated the reliability of Vc so far. Lohr et al. [27] investigated the within and between-day reliability of Vc in the lumbar erector spinae muscle of healthy females and males, using this formula: Vc = 0.8*Dm / Tc. Vc in this study showed an excellent relative (intraclass correlation coefficient ICC > 0.90) and absolute (coefficient of variation CV < 8%) reliability. De Paula Simola et al. [28] investigated the between-day reliability of the following two formulas to calculate Vc in twenty male sports students: V_10_ = 0.1*Dm / t_10%_ and V_90_ = 0.9*Dm / t_90%_ [28]. Absolute reliability was higher in rectus femoris (RF) and biceps femoris (BF) (CV < 10%) compared to gastrocnemius lateralis (CV = 12.3% and CV = 11.3% for V_10_ and V_90_, respectively) [28]. Both formulas showed excellent relative reliability in all three muscles (ICC > 0.90) [28]. In addition to the formulas used in the two studies mentioned, two other formulas to calculate Vc have been frequently reported: Vc = Dm / (Td +Tc) [29] and Vc_rn_ = 0.8 / Tc [30]. The reproducibility of Vc calculated by these two formulas is still unclear. Therefore, information on the reproducibility of these two formulas is needed. Further, a direct comparison of all five formulas for calculating Vc in terms of their reproducibility within the same sample would help reach a consensus on a standardized approach.

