Differences exist not only regarding the formulas used to calculate Vc, but also regarding the electrical stimulation procedure to determine the radial displacement curve from which Vc is calculated. In a systematic review about the reliability of TMG, Martín-Rodríguez et al. [1] found that previous studies mainly used an inter-stimulus interval (ISI) of 10 s or 15 s to avoid fatigue or post-tetanic potentiation. But they also stated a lack of studies investigating the optimal rest interval between consecutive stimuli [1]. To our knowledge, only two studies investigated the effect of different ISI on tensiomyographic parameters so far. One study investigated the effect of different ISI (30 s, 10 s, 5 s) on Dm and Tc of the RF muscle during ten consecutive stimuli at a constant intensity (50 mA) [31]. The results showed that Tc was not significantly affected by different ISI, whereas Dm was significantly greater using an ISI of 10 s than 30 s [31]. Notably, Tc decreased significantly during ten consecutive stimuli, irrespective of the ISI, whereas Dm was not affected [31]. However, Latella et al. [32] found no significant effect of ISI (10 s, 20 s) on Dm or Tc of the biceps brachii muscle. Consequently, they concluded that an ISI of 10 s is sufficient during five consecutive stimuli [32]. However, both of the studies mentioned above did not report Vc, so the effect of ISI during repeated stimulation on Vc is still unclear.

Therefore, the first aim of this study will be to investigate the within and between-day reliability of five different formulas to calculate Vc. The second aim will be to investigate the effect of different ISI during repeated stimulation on Vc, assessed by the example of M. biceps femoris and M. rectus femoris. We hypothesize that Vc will be affected by changing ISI during ten repeated stimuli at a constant intensity of 50 mA.

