### Statistical analysis

We will report Vc_0-10%_, Vc_0-90%_, Vc_10-90%_, Vc_norm_ and Vc_Dm/t90%_ for both the RF and BF descriptively as mean (M) and standard deviation (SD). All data will be checked for outliers via visual inspection of boxplots. Outliers will be defined as data points outside of three times the interquartile range. The normal distribution of all variables will be tested using the Shapiro-Wilk Test. To assess a systematic bias between M1-M2 and M1-M3, we will perform a two-tailed paired t-test, respectively [47].

For the assessment of relative reliability, we will calculate intra-class correlation coefficients (ICC, mean rating (k = 2), absolute agreement, two-way mixed-effects model) with 95% confidence intervals (CI) [48]. ICC scores lower than 0.5, between 0.5 and 0.75, between 0.75 and 0.9 or greater than 0.9 will be interpreted as poor, moderate, good or excellent reliability [48].

Absolute reliability will be quantified by calculating the standard error of measurement (SEM and SEM%), the minimal detectable change (MDC and MDC%) [49] and the CV [47], including the respective 95% CI’s. The SEM indicates the estimation precision of a measure and will be calculated as SEM = SD * √1-ICC [47]. The SEM% allows a comparison of different Vc calculations as it is unitless and will be calculated as SEM% = (SEM / M)* 100 [50]. The MDC presents the smallest difference between two measures that can be differentiated from measurement error and hence may be considered real [49]. Following Weir et al. [49], we will calculate the MDC as MDC = SEM * 1.96 * √2. The MDC% will be calculated as MDC% = (MDC/M) * 100 [50] to allow a comparison between different calculations of Vc independently of units. The CV will be calculated as CV = SD / M * 100 [47], whereby SD refers to the standard deviation and M to the mean of individual differences between M1 and M2 or M1 and M3. A CV > 10% will be interpreted as insufficient reliability with reference to previous studies investigating the reliability of tensiomyographic parameters [27, 51, 52].

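### The protocol promises a direct comparison of the five Vc formulas, but plans only separate per-formula estimates and no paired estimate of a between-formula difference

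*Protocol article*

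**What the plan says.** The Introduction gives the motivation: "a direct comparison of all five formulas for calculating Vc in terms of their reproducibility within the same sample would help reach a consensus". It then words the first aim as estimation: "the first aim of this study will be to investigate the within and between-day reliability of five different formulas to calculate Vc". The Discussion goes further: "This study will compare the five most frequently used formulas to calculate Vc regarding their within and between-day reliability", and later "Thereby our results will allow a direct comparison between these formulas in terms of their reproducibility". The Abstract makes a similar promise.

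For each formula, the Statistical analysis section plans:
- paired t-tests for systematic bias (M1-M2 and M1-M3);
- an ICC ("mean rating (k = 2), absolute agreement, two-way mixed-effects model") with 95% CI and a verbal category;
- SEM, SEM%, MDC, MDC% and CV with their own 95% CIs, and a 10% cut-off for the CV.

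The basis offered for comparing formulas is the absence of units. For SEM%: "The SEM% allows a comparison of different Vc calculations as it is unitless". For MDC%: "to allow a comparison between different calculations of Vc independently of units". No difference or ratio between formulas is estimated, and no rule says when one formula counts as more reproducible. In the repeated-measures ANOVA the formulas are separate dependent variables, not a factor.

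**The concern.** Removing units puts the formulas on one scale, but it deals with neither sampling error nor pairing. Every formula is built from the same Dm, Td and Tc, so the measurement errors of the formulas are correlated, and the contrast between two formulas can be known more precisely than either value alone. Separate estimates with separate intervals do not use that.

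A reader who wants the promised comparison then has two informal routes. One is to order the point estimates, which always yields a best formula, even if none exists. The other is to see whether the intervals overlap, which is very conservative for paired data. The ICC categories and the CV cut-off do not close the gap, because two formulas on opposite sides of a threshold need not differ. The results are meant to support a standardised approach, so the distinction matters.

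**Working it through.** **1. The plan's own precision figure.** Inputs from the Sample size justification: ICC 0.92, k = 2, alpha 0.05, interval width 0.15. Bonett's formula:

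n = 8 z² (1−ICC)² (1+(k−1)ICC)² / (k(k−1) w²) + 1 = 8 × 3.8415 × 0.0064 × 3.6864 / (2 × 0.0225) + 1 = 17.11, rounded up to 18.

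This matches the stated 18. It covers the precision of one ICC. The second calculation covers the ISI effect. Neither concerns a difference between formulas.

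**2. Single intervals at n = 24.** F-based 95% CIs for the mean-of-two ICC are 0.904–0.982 when the single-measure ICC is 0.92, and 0.813–0.965 when it is 0.85. They overlap widely.

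**3. Interval of an SEM.** With 23 df, the factors are √(23/χ²₀.₉₇₅) = 0.78 and √(23/χ²₀.₀₂₅) = 1.40. Two separate intervals are disjoint only if the observed SEM ratio exceeds 1.40/0.78, about 1.8.

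**4. Separate intervals against a paired test.** Simulated M1-M2 differences for two formulas, n = 24, normal errors, true SEM ratio 1.4. The error correlation is not in the document and is assumed. Ranges reflect simulation noise.

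| Error correlation | Separate CIs disjoint | Pitman-Morgan, two-sided 5% | Point estimates in wrong order |
|---|---|---|---|
| 0.7 | about 5% | 58–59% | 1.6% |
| 0.9 | 0.4–0.5% | 92% | 0.05% |

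A hand check of the paired test uses the correlation between the sum and the difference of the two formulas' errors, (1.96 − 1)/√(2.96² − 4ρ² × 1.96). This is 0.433 at ρ = 0.7 and 0.618 at ρ = 0.9. On Fisher's scale, times √21, these become 2.12 and 3.31. Against 1.96 the power is about 57% and 91%, in line with the simulation. Against 2.64 (alpha 0.05/6, for six pairs) it is about 30% and 75%.

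**5. Chance spread.** Four formulas with identical true SEM: the largest-to-smallest ratio has median 1.20 to 1.29 and 90th percentile 1.35 to 1.53, at assumed correlations 0.8 and 0.5.

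**6. The same question on the ICC scale.** Assumed true-score correlation 0.9, error correlation 0 to 0.8. For true ICCs 0.92 and 0.85, separate CIs are disjoint in 0.1–1.9% of studies. For 0.92 and 0.90, point estimates give the wrong order in 23–31%.

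**7. How many formulas can differ.** Vc_0-90% = 0.9 × Dm/(Td + Tc) = 0.9 × Vc_Dm/t90%. A constant multiplier scales SD and mean alike, so ICC, SEM%, MDC% and CV are identical for these two. Four distinct formulas remain, which gives 4 × 3/2 = 6 pairs. MDC% is 1.96 × √2 = 2.77 times SEM%, so it orders formulas exactly as SEM% does.

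**8. Small-sample behaviour of a bootstrap.** A simple percentile interval for the SEM ratio at n = 24 excludes no difference in about 7–8% of studies in which the true SEMs are equal.

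**The case against.** The strongest reply is that the first aim is to estimate reliability, that the only hypothesis concerns ISI, and that same-sample, unit-free estimates with intervals already permit a descriptive comparison. Much of this stands. A reader might infer that the study cannot answer its first aim. The document does not support that: the aim as worded is met by the planned estimates. A reader might also infer that formulas will be ranked by point estimate or by interval overlap. The protocol states neither rule; its stated interpretation is per formula, through ICC bands and the CV cut-off. The figures above therefore show what informal readings would do, not an error the plan commits.

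A second reply is that pairing helps less than it seems. At a true ratio of 1.4, point estimates rarely give the wrong order. At ratios 1.2 and 1.1 with correlation 0.7 they do so in about 11% and 26% of studies, but there the paired test detects only 22% and 9%. This is true, and it means that small differences will stay unresolved. Showing that openly is still better than leaving an unqualified ordering.

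A third reply is that the raw data and code will be public, so paired intervals can be added later. They can, but the study is to be preregistered, and a rule chosen after the results are known carries less weight.

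What does not stand is that a descriptive comparison is what the text announces. It says the study will compare the formulas and never labels that comparison descriptive. Nor is this merely detail held elsewhere, since the section specifies its statistics fully and names what the comparison rests on.

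**Conclusion.** The point holds in moderate form: a comparison is announced as a product of the study, the analysis contains no estimate of a between-formula difference, and the pairing that the design provides is unused. No planned statistic is made invalid by this.

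For one pair with a true SEM ratio of 1.4, the loss is between about 5% and 58–59% detection at correlation 0.7, and between 0.4–0.5% and 92% at 0.9. Adjustment for six pairs narrows that advantage but does not remove it.

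These sizes rest on 24 complete participants, normal errors and assumed correlations. They also take the SEM from the SD of paired differences, whereas the plan computes it from the SD and the ICC. The true correlations and the true SEM ratios are unknown.

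**What to change.** Add to the Statistical analysis, for each muscle and for M1-M2 and M1-M3:

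- A paired 95% CI for the between-formula ratio of SEM%, named as the single lead metric. Resample participants, with the same resample for all formulas.
- An interval with checked small-sample coverage, for example bias-corrected or studentised on the log scale. A Pitman-Morgan test on mean-scaled differences is an alternative; it compares the random error only and leaves out any systematic shift. The simple percentile interval is too narrow at n = 24.
- Comparison of the four distinct formulas only, with a sentence that Vc_0-90% and Vc_Dm/t90% are proportional and so have identical reliability.
- Adjustment for the six pairs within each muscle and interval, for example Holm, or intervals at 1 − 0.05/6 = 99.2%. One metric over two muscles and two intervals gives 6 × 2 × 2 = 24 contrasts; making ICC a second decision metric would double that to 48, so report ICC differences as supportive.
- A rule: call one formula more reproducible only when the adjusted interval excludes 1.

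If the authors prefer not to add this, the Abstract and Discussion should call the comparison descriptive.

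The cost is a short piece of R code and one extra table, with no new data. The downside is that some apparent rankings will be reported as unresolved.
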